#### Outcomes

Outcome variables will be tested for normal distribution by use of the Kolmogorov-Smirnov test and by further descriptive statistics. Normally distributed continuous variables will be given as mean [with standard deviation (SD)], variables with skewed distribution as median with interquartile range, and categorical variables as percentages. For parametric procedures all skewed distributed continuous parameters will be logarithmically transformed (log10). Analysis of covariance, adjusted for the respective baseline values, will be used to analyze the continuous primary and secondary outcome variables.

All statistical tests to assess the treatment difference between eplerenone and placebo will be performed using a 2-sided hypothesis test at 5% significance level. Data will be analysed using SPSS 17.0 statistical package (SPSS, Inc., Chicago, IL, USA).

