**Methods/design:**

Overall, 110 adult male and female patients with primary hyperparathyroidism will be randomly assigned to eplerenone (25 mg once daily for 4 weeks and 4 weeks with 50 mg once daily after dose titration] or placebo, over eight weeks. Each participant will undergo detailed clinical assessment, including anthropometric evaluation, 24-h ambulatory arterial blood pressure monitoring, echocardiography, kidney function and detailed laboratory determination of biomarkers of bone metabolism and cardiovascular disease.

The study comprises the following exploratory endpoints: mean change from baseline to week eight in (1) parathyroid hormone(1–84) as the primary endpoint and (2) 24-h systolic and diastolic ambulatory blood pressure levels, NT-pro-BNP, biomarkers of bone metabolism, 24-h urinary protein/albumin excretion and echocardiographic parameters reflecting systolic and diastolic function as well as cardiac dimensions, as secondary endpoints.

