## Methods/design

### Study design, endpoints and safety

EPATH is a single-center, double-blind, placebo-controlled, randomized, parallel group trial. Patients with PHPT diagnosed according to the report of the 3rd International Workshop on Diagnosis of PHPT will be screened for inclusion into the study
[14]. Patients diagnosed with symptomatic/asymptomatic PHPT will be consented and screened for eligibility to participate in the EPATH trial. Overall 110 patients will be randomized to receive eplerenone or placebo in a 1:1 ratio (55 patients will receive eplerenone and 55 patients will receive placebo).

The design, conduction and reporting of the EPATH study adheres to the recommendations of the CONSORT Statement (
http://www.consort-statement.org/). The study will be performed in accordance with the Good Clinical Practice (GCP) guidelines and the Declaration of Helsinki. The study has been approved (N° 24–032 ex 11/12; EudraCT number: 2011-005683-21) by the Ethics Committee of the Medical University of Graz, Austria.

The primary endpoint of the study is to evaluate the efficacy of eplerenone relative to placebo to reduce PTH(1–84) concentration, measured by two different laboratory methods, in patients with PHPT. Secondary endpoints are the mean changes from baseline after 8-weeks with eplerenone versus placebo, in the following measurements: (1) 24-hour systolic and diastolic ambulatory blood pressure (ABP) levels; (2) biomakers of CVD; (3) biomarkers of bone metabolism: osteocalcin, β-crosslaps, bone alkaline phosphatase and tartrate-resistant acid phosphatase; (4) 24-h urinary albumin/protien excretion; and (5) echocardiographic parameters related to systolic and diastolic function as well as cardiac dimensions (i.e. left ventricular ejection fraction, E/E´ ratio, left ventricular end-diastolic/systolic pressure/volume/index and LV posterior wall thickness).

We decided to evaluate the effect of MR-blocker eplerenone on iPTH(1–84) - the primary outcome – and on CV and bone health – the secondary outcomes - after 8 weeks because (1) preliminary data from the Graz Endocrine Causes of Hypertension (GECOH) study suggest that MR-blockade with eplerenone might exert “rapid” effects on iPTH(1–84) levels
[15]; (2) eplerenone has been shown to significantly lower BP after a few days of treatment, indicating that this dose may be sufficient to impact on iPTH(1–84) levels

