### Statistical methods

#### Sample size calculation

Sample size calculation for the primary endpoint iPTH(1–84) is based on (1) an observed effects of eplerenone treatment (and adrenalectomy) on iPTH(1–84) levels in a previously published study
[25]; (2) the proven significant association between (elevated) PTH levels on risk of fatal cardiovascular events in humans
[3]; and (3) data derived from patients, which have been managed at the outpatient clinic of the Division of Endocrinology and Metabolism at the Medical University of Graz, with primary hyperparathyroidism.

Based on the observational data from the GECOH study, MR-blockade (by eplerenone and spironolactone) in patients with primary aldosteronism was associated with an approximate 10.0 pg/mL decrease in PTH levels after a mean follow-up of 12 months
[25]. However, two patients at short-term follow-up of 4 weeks revealed a similar decrease of PTH levels with MR-blockade compared to long-term follow-up, indicating a rapid effect of MR-blockade on PTH levels. We are, however, aware that due to limited evidence regarding the effects of eplerenone in patients with PHPT, final conclusions cannot be drawn.

We further evaluated whether an increase of 10.0 pg/mL PTH is translated into a significant higher risk of CV mortality. In the LURIC study comprising 3.300 patients referred to coronary angiography the increment of 10 pg/mL PTH was significantly related to a 4% [Hazard Ratio (95% CI): 1.04 (1.03-1.06) p < 0.001] higher risk of cardiovascular death
[3]. We assumed an effect size of 10.0 pg/mL, assuring sufficient power to decrease PTH by eplerenone 25/50 mg once daily. Thus, for a two-sided alternative-hypothesis with an α of 0.05 and a power (1-β) of 80% we calculated a sample size of 51 study participants per group. To compensate for drop-outs during the study (estimated to around 10%) we plan to enrol 55 patients per group.

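### A normality check on the trial's own outcome data decides whether the primary PTH result is a pg/mL difference or a ratio, although the endpoint and sample size are set in pg/mL

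*Protocol article*

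**What the plan says.** Three parts of the protocol article bear on the scale of the primary analysis.

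- **Abstract, Methods/design.** The endpoint is the "mean change from baseline to week eight in (1) parathyroid hormone(1–84) as the primary endpoint". The main text (Study design, endpoints and safety) is looser and gives no scale: "The primary endpoint of the study is to evaluate the efficacy of eplerenone relative to placebo to reduce PTH(1–84) concentration".
- **Sample size calculation.** The target is absolute: "We assumed an effect size of 10.0 pg/mL", with two-sided α 0.05 and 80% power, giving 51 per group and 55 enrolled.
- **Outcomes.** First a check: "Outcome variables will be tested for normal distribution by use of the Kolmogorov-Smirnov test and by further descriptive statistics". Then the rule: "For parametric procedures all skewed distributed continuous parameters will be logarithmically transformed (log10"). Then the model: "Analysis of covariance, adjusted for the respective baseline values, will be used to analyze the continuous primary and secondary outcome variables".

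ANCOVA is a parametric procedure and PTH is continuous, so the transformation rule governs the primary analysis. Nothing exempts PTH from it, fixes the scale for PTH, or says whether the ANCOVA response is the week-8 value or the change.

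**The concern.** The protocol does not leave the scale open for a later document. It states a rule, and the rule ties the scale to data that will be seen only in the trial. Three consequences follow.

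1. **The effect measure is not fixed.** One branch estimates a mean difference in pg/mL, which is what the Abstract defines and the sample size assumes. The other estimates a ratio of geometric means, which is neither.
2. **The trigger is loose.** The version of the Kolmogorov-Smirnov test, its threshold and the weight of the accompanying descriptive summaries are not given. Two competent analysts could reach different scales from the same data, which leaves room for selective choice.
3. **The check looks at the wrong thing.** ANCOVA's distributional assumption concerns the residuals given arm and baseline, not the distribution of the outcome itself.

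At stake are the interpretability of the primary result, possibly its significance, and some power.

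**Working it through.** **1. The plan's own figure.** n per group = 2(z₀.₉₇₅ + z₀.₈₀)² × SD² / δ², with δ = 10 pg/mL. Since (1.960 + 0.842)² ≈ 7.849, n = 0.157 × SD². No SD is given; the section cites "data derived from patients, which have been managed at the outpatient clinic of the Division of Endocrinology and Metabolism" without a number. Solving backwards, n = 51 needs an SD of 17.85–18.02 pg/mL (normal approximation) or 17.68–17.85 (t-test). At SD 18, n = 50.9, rounded up to 51. The figure can be back-solved but not reproduced, and whether this SD describes a level or a change is unknown. Either way it is a pg/mL calculation.

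**2. The target on the other scale.** A fall of 10 pg/mL from baseline B is the ratio (B − 10)/B. The baselines are assumed.

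| B (pg/mL) | Ratio | log10 difference |
|---|---|---|
| 80 | 0.875 | −0.058 |
| 100 | 0.900 | −0.046 |
| 150 | 0.933 | −0.030 |
| 200 | 0.950 | −0.022 |

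If log10 is triggered, the planned effect corresponds to no single target.

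**3. How stable the trigger is.** Simulation: 51 per arm, 2,000 trials per setting, no treatment effect. Assumed, not from the documents: lognormal PTH, median 100 pg/mL, baseline/week-8 correlation 0.8, and a mechanical p < 0.05 switch. Share of trials in which non-normality is declared:

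| Log-SD | Uncorrected test, week-8 PTH | Lilliefors version, week-8 PTH | Lilliefors version, change |
|---|---|---|---|
| 0.15 | 0.4% | 17% | 6% |
| 0.2 | 1% | 32% | 7% |
| 0.3 | 6% | 60% | 16% |
| 0.4 | 18% | 83% | 33% |
| 0.5 | 43% | 96% | 60% |

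The same population can land on either scale, depending on the sample, the version of the test and the variable tested.

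**4. Raw versus log ANCOVA when there is an effect.** 51 per arm; all distributional inputs are assumed; r is the baseline/week-8 correlation.

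| Setting | Power raw | Power log | Disagree on p < 0.05 |
|---|---|---|---|
| Change SD 16–20 pg/mL (log-SD 0.25–0.3, r 0.7), proportional effect | 94%, 81%, 80% | 95%, 83%, 82% | 2%–6% |
| Log-SD 0.3, r 0.8, 10% reduction | 79% | 83% | 7% |
| Log-SD 0.4, r 0.8, 10% reduction | 55% | 60% | 12% |
| Log-SD 0.5, r 0.8, 10% reduction | 35% | 41% | 14% |
| Log-SD 0.6, r 0.85, 15% reduction | 61% | 73% | about 17%–18% |

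For proportional effects, fixing the log scale gains roughly 1 to 11 points (11 to 12 at the heaviest skew, depending on the run). If the drug instead subtracts a constant 10 pg/mL (median 100, r 0.8, log-SD 0.3–0.5), the gap widens to about 10–18 points and disagreement to 11%–20%. The size is clearly driven by assumptions.

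**5. Type I error.** In the settings of step 3, the analysis on the test-selected scale rejected in 3.6%–6.1% of trials, close to the fixed raw and fixed log analyses in the same runs. No inflation is seen.

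**6. Is the log branch workable?** Write W for week 8, B for baseline and g for arm. W − B = a + bB + τg is the same model as W = a + (b + 1)B + τg, so τ and its p-value are identical. The same holds with log W and log B. ANCOVA of log week-8 PTH on log baseline is therefore an analysis of change in log PTH.

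**The case against.** The strongest reply is that the plan is workable and does no demonstrated statistical damage. Checking for skewness and taking logs is common practice, type I error stays near 5%, and where the change SD is near the roughly 18 pg/mL implied by 51 per group, the two scales differ by only 1 to 2 points of power and disagree in 2%–6% of trials. The larger figures come from heavier assumed skew. The simulated switch is also more mechanical than the written rule, which adds descriptive summaries. All of this stands, and it limits the size of the point.

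A reader might infer that the log rule cannot be applied to a change-from-baseline endpoint, because about half of the changes are zero or negative without a treatment effect, and that about half of the patients would be lost. The document does not support this. It transforms continuous parameters and adjusts for baseline; nowhere does it instruct anyone to take the log of a difference. Log week-8 PTH with log baseline is the natural reading, and step 6 shows that it is a proper change analysis.

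It could also be said that the Abstract calls the endpoints exploratory and that scale is a matter for the analysis plan. The first does not settle it, since one endpoint is named primary, powered and tested at 5%. The second holds for the scale of each secondary variable, which is not raised here. It does not hold for PTH, where the protocol itself lays down a data-dependent rule.

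**Conclusion.** The point stands as a fault in a stated rule. The effect measure of the primary analysis depends on a loosely defined look at the trial's own outcome distribution, while the endpoint and sample size are expressed on the absolute scale. The check is also directed at the outcome and not at the residuals. This part needs no assumption about PTH.

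The size does. With lognormal PTH, 51 per arm and a proportional effect, the power at stake is roughly 1 to 11 points and the scales disagree on significance in roughly 2%–18% of trials. The low end applies near the implied SD of about 18 pg/mL; a constant absolute effect could go beyond the high end. A reader might infer a false-positive problem from the words data-dependent; the simulations do not show one. The harm is an effect measure chosen by the data, scope for selective choice of scale, and some lost power if PTH is clearly skewed. It should be corrected, and the correction is one of wording.

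**What to change.** Remove the normality pre-test for the primary endpoint and pre-specify one response and one scale for PTH. One sound choice:

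- ANCOVA of log week-8 PTH on arm and log baseline PTH, reported as a geometric mean ratio with 95% CI;
- the pg/mL ANCOVA as a sensitivity analysis;
- the target effect and power basis restated on the log scale, with the baseline PTH used for the translation and the assumed SD given.

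Fixing pg/mL as the primary scale would also cure the fault and would match the existing sample size basis, at some cost in power if PTH is skewed. What matters is that the choice is made before outcome data are seen.

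Cost: a change of wording, with no new visits, measurements or patients called for by the change itself. With the log scale, the headline effect becomes a percentage, and the 10 pg/mL target must be translated at a stated baseline, since it means a 12.5% reduction at 80 pg/mL but only 5% at 200. A pg/mL estimate can still be shown beside it.

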## Discussion

In view of the potential interrelationship between aldosterone and PTH in patients with PHPT we hypothesize that the inhibition of aldosterone mediated effects by MR-blockade with eplerenone in PHPT patients not undergoing surgery will (1) result in a decrease of PTH(1–84) levels, (2) lead to beneficial effects on bone metabolism and (3) exerts beneficial effect on CV health and kidney function. Thus, the EPATH trial is the first clinical trial to specifically examine the effects of MR-blockade on PTH levels, bone, renal and CV health in patients with PTPH not undergoing surgery.

The “Third International Workshop on Asymptomatic Primary Hyperparathyroidism” concluded that further studies are definitely warranted in those patients with PHPT in whom surgery is not recommended (or indicated)
[26]. This is of particular importance considering that even asymptomatic PHPT is associated with higher CV morbidity and mortality. To date, little is known about the mutual interaction between these two hormones and its potential role for target organ damage. In experimental rat studies combined 5/6 nephrectomy and parathyroidectomy resulted in decreased aldosterone levels compared to control rats
[27]. Studies in PHPT patients noted markedly decreased plasma aldosterone levels and plasma renin activity after parathyroidectomy
[28,29]. In a larger study, Brunaud et al. reported in patients with PTH excess after parathyroidectomy significantly decreased aldosterone and BP levels
[30].

Recently, Maniero et al. impressively demonstrated the expression of the MR in both PTH-secreting adenoma and in normal parathyroid gland tissue
[31]. Interestingly, the MR was predominantly located in the nucleus of the parathyroid cells, indicating that aldosterone (and cortisol), participate in a “tonic” regulation of PTH synthesis and secretion. It is one crucial aim of the EPATH trial to evaluate whether eplerenone inhibits the modulation of PTH secretion and synthesis of aldosterone and cortisol. In fact, cortisol is also suggested to activate the MR, particularly in conditions of an increased reactive oxygen species generation
[32]. Moreover, plasma cortisol levels increase after PTH infusion and cortisol is suggested to participate in the regulation of PTHrP expression
[33,34]. In addition, we cannot exclude the possibility that MR blockade can directly inhibit PTH secretion independent of aldosterone and cortisol. Finally, it is unclear whether eplerenone inhibits some of the non genomic effects of aldosterone (and cortisol)
[17].

Findings from previous studies support the notion that PTH may stimulate adrenal aldosterone synthesis directly. The identification of the PTH/PTH-RP receptor (PTH1R) in human and rat adrenal cortex binds intact PTH and the biologically active N-terminal fragment PTH 1–34 and provides an indication for direct effects of PTH on ZG cells
[35]. Mazzocchi et al. and others found that PTH and PTH-related protein increase in human adrenals aldosterone production by binding to the PTH/PTH-RP receptor
[11,12]. In isolated rat ZG cells exposed to PTH(1–84) and PTH(1–34) Olgaard et al. observed a 2-fold increased of aldosterone release resulting from PTH induced Ca^2+^ionophore-like effects
[36]. Thus, PTH might directly mediate aldosterone production by inducing calcium entry in adrenal ZG cells via binding to PTH/PTH-RP receptors, voltage-gated L-type calcium channels and by activating various signal transduction pathways and indirectly by activating the renin–angiotensin system. Figure
2 summarizes the suggested pathways of an interplay between PTH and the renin-angiotensin-aldosterone system. With the EPATH trial we aim to evaluate whether the blockade of aldosterone by eplerenone breaks through the stimulating effects of PTH on aldosterone secretion by decreasing aldosterone mediated renal calcium loss and subsequently enhanced PTH secretion. 

**Figure 2 F2:**
[figure not shown]
**Overview of the bidirectional interplay between aldosterone and PTH.** Calcium influx is crucial for activating the synthesis of renin in juxta glomerular cells and aldosterone in zona glomerulosa cells. Renal renin synthesis is mainly controlled by tubular sodium concentration, arterial blood pressure and the sympathetic nervous system. PTH is suggested to stimulate renin synthesis by increasing calcium levels in JG cells. Extracellular potassium, adrenocorticotropic hormone and angiotensin II are major stimulators of aldosterone synthesis in the adrenal glands. Both factors interact with voltage-gated calcium channels and depolarize the zona glomerulosa cells, which results in elevated intracellular calcium levels. PTH might directly stimulate aldosterone synthesis by binding to the PTH1R and adrenocorticotropic hormone receptor. In addition, PTH is suggested to increase sensibilization of angiotensin II, which by itself reduces cellular calcium extrusion through activating Na+/Ca–exchangers in zona glomerulosa cells. Aldosterone in turn facilitates renal and fecal calcium loss resulting in further PTH secretion.

Several cross-sectional and prospective studies documented a strong relationship between both elevated PTH and aldosterone levels, respectively and arterial hypertension as well as increased arterial stiffness
[37-40]. Accordingly, one might speculate that the interplay between both hormones aggravates BP elevation, and remodeling of blood vessels in patients with elevated PTH
[41]. This hypothesis would be in line with the observation of Morfis et al. that aldosterone levels are strongly related to systolic and diastolic ABPM values. However, the correlation is less significant if PTH is considered as confounder
[42]. In addition, PTH mediated intracellular and mitochondrial calcium overload results in a disturbed redox status in various tissues i.e. in cardiac myocytes, resulting in increased oxidative stress
[43]. These mechanisms might in part explain the significant relationship between circulating aldosterone and PTH levels and higher risk of left ventricular hypertrophy and sudden cardiac death in patients at high CV risk
[3,8,44]. Importantly, aldosterone induced urinary and fecal Ca^2+^ and Mg^2+^ excretion was attenuated by spironolactone. Furthermore, intake of MR-blockade resulted in reduced intracellular calcium overload and improved redox status in peripheral blood mononuclear cells
[13]. The above data suggest that through its calcium wasting properties aldosterone might activate the PTH-cascade resulting in further target organ damage, which might be reversed by MR-blockade. In the EPATH study we aim to evaluate whether MR-blockers with eplerenone has effects on 24-h ambulatory arterial blood pressure, NT-pBNP, kidney function, LV function and structure in patients with PTH excess.

Increased aldosterone mediated renal calcium loss might be the key mechanisms for the subsequent development of hyperparathyroidism in chronic heart failure (HF). The majority of studies demonstrated calcium wasting properties of aldosterone, independent of PTH, particularly in the setting of dietary salt excess
[45,46]. In rats treatment with aldosterone/1% NaCl causes increased urinary and fecal Ca^2+^ and Mg^2+^ excretion, hypocalcemia, hypomagnesemia and consequently secondary hyperparathyroidism, as well as increased tissue calcium concentration. Due to increased PTH activity bone mineral density and strength were significantly reduced. Accordingly, HF patients suffering from secondary aldosteronism and PTH excess are at significantly higher risk of orthopedic fractures, in particular hip fracture, compared to controls
[47]. In contrast, treatment with the MR-blocker spironolactone prevented reduction of bone mineral density in aldosterone/salt/loop diuretics treated rats
[48]. However, studies in humans that evaluated the association between MR-blocker use with fracture risk are rare. One study documented that spironolactone use was inversely associated with total fracture risk (odds ratio: 0.575; 95% CI: 0.346 to 0.955, p = 0.0324) in men with congestive HF
[49]. Treatment with the MR-blocker spironolactone was inversely related to fractures in chronic HF males. It remains (however) to be determined by adequately designed placebo controlled randomized trials whether MR-blockade affects bone metabolism and fracture risk in various risk groups. In the EPATH trial we attempt to evaluate the effects of aldosterone on bone metabolism reflected by laboratory markers of bone metabolism in patients at PTH excess. Considering the above mentioned evidence, interventional studies are urgently needed to evaluate the effects of MR-blockade on bone mineral density and bone metabolism in chronic HF patients.

The majority of experimental animal and human studies identified a clinically relevant interplay between aldosterone and PTH levels. The bidirectional stimulatory effects of PTH and aldosterone may potentiate the risks of development and progression CV and bone, kidney disease in patients with PHPT. It has been suggested that treatment of either disease, aldosterone excess and hyperparathyroidism, might positively affect the CV system by decreasing the activity of both hormone systems. In view of the potential interrelationship between aldosterone and PTH in patients with PHPT the findings from the EPATH study will facilitate our understanding of the putative benefits of eplerenone in patients with PTH excess, and the mechanisms between both hormone systems.

